**Figure 4 F4:**
[figure not shown]
Mobile/fixed clinics service workflow. ART, antiretroviral; BSID, Bayley Scales of Infant Development; DoH, Department of Health; PrEP, pre-exposure prophylaxis; REDCap, Research Electronic Data Capture; SA_ID, South Africa national identification number; STI, sexually transmittedinfection.

Clinical procedures: Irrespective of whether they consent to the study, all eligible individuals attending clinics are offered confirmatory HIV testing, with two point of care tests and then blood sent to laboratories for ELISA testing (**Genscreen** ULTRA HIV Ag-Ab qualitative immunoassay (fourth Generation) Bio-Rad, Marnes-la-Coquette, France). Individuals who test HIV-negative receive counselling around the benefits of PrEP and HIV-positive individuals receive counselling around the benefits of immediate starting of ART. If they agree, they will undergo clinical screening for PrEP and ART. Screening includes Point of Care tests for creatinine (StatSensor-I create-test strips, Nova Biomedical UK) to assess renal function and hepatitis B (Alere Determine HBsAg, Alere International Limited, Ballybrit, Galway, Ireland; Architect i2000 analyzer, Abbott Diagnostics, Abbott Park, Illinois, USA), with vaccination offered to those who are negative, and sexual behaviour questionnaire to assess eligibility.

If HIV positive, ART is started by the professional nurses in any of 11 PHCs in the study sites. Patients who are eligible for PrEP are started in the three PrEP providing clinics (the mobile vans or the fixed urban adolescent and youth friendly clinic). Persons who are not eligible for PrEP receive counselling and, as indicated, a clinic referral with the screening results. A professional nurse initiates PrEP or ART usually on the same day or within 2 weeks of the screening visit. The professional nurse provides PrEP counselling that includes (1) *sexual health promotion,* with an emphasis on tackling the multiple health-related behaviours that will affect fertility and sexual pleasure (sexually transmitted infections, mental health, alcohol, diet and exercise); (2) assessment of fertility desire and contraception counselling; (3) choice of contraception and condoms; (4) HIV-negative men are also counselled around the benefits of VMMC and referred accordingly.

The counsellors provide counselling on adherence and develop an individualised adherence plan with the offer of face-to-face or virtual (WhatsApp/text based) adherence support. If the participant agrees to immediate PrEP initiation, s/he is issued with a month’s supply of generic tenofovir disoproxil fumarate and emtricitabine. Baseline and follow-up bloods are taken and processed as per SA National Department of Health guidelines. The professional nurse registers the participant at the clinic (or updates the record if the participant is already registered) so that the participant’s records are available should the participant seeks care there. Participants receive a phone call 7 days after initiating PrEP to complete a standard symptom screen for adverse effects and be referred to clinic for care if necessary. Participants have a clinic appointment scheduled 1 month, after PrEP initiation, as per national guidelines; appointments for refills and monitoring will be quarterly thereafter through either the mobile clinic, or other community-based refill points. Neutral text message reminders are provided for participants who have access to private messaging and phone calls. Participants are able to reschedule their appointments by text message, WhatsApp or calling the clinical hotline. Contact information is provided for the clinics whom participants can contact at any time.

### Randomisation

We defined cluster as a pair of peer navigator (PN) who live and work in one of the 24 administrative areas that were included in the trial. Peer navigators were preassigned to 24 areas before the randomisation process. Using data from our recent Determined, Resilient, Empowered, AIDS-free, Mentored and Safe (DREAMS, combination HIV prevention) Impact Evaluation study which collected data from a representative sample of young women residing in the study areas, a restricted randomisation was applied to get balanced covariates (location, HIV testing prevalence and uptake of DREAMS combination HIV prevention by adolescent girls and young women) across the three arms. We generated a random set of possible 100 000 allocation options. After applying all three restrictions, a total of 47 924 possible allocations remained, and a random number was generated and assigned to each allocation option. The random numbers were ranked from lowest to highest and the allocation option with the first rank was then selected. A randomisation list with intervention arms named alphabetically (A, B and C) was generated.

Following the statistical randomisation, a public randomisation was conducted where peer navigators were divided into three groups (A, B and C). Each group had 16 allocated PNs and three floating ones. Each group chose a suitable name and a leader who represented them. Group leads picked a concealed number to determine the order of picking their study arm from a box. The facilitator shook the box so to make sure that each concealed arm in the box had an equal chance of being picked. Lastly, the leaders were asked to open and announce the arms of their respective groups to the bigger group.

### Blinding

The statistician and clinical staff did not participate in the public randomisation with peer navigators and they will remain blinded until the results of the study have been finalised.

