### Study recruitment and procedures

Study recruitment: Peer navigators are a cadre of recently matriculated youth or college graduates aged 18 to 30 years (male and female) recruited from the research community through the local municipal and traditional leaders. Between June 2018 to September 2018 participants underwent a 20 week training programme (3 days a week) which covered, youth development, HIV and sexual health information, HIV counselling and testing, confidentiality, ethics and research methods, study procedures and HIVST. Progress was evaluated using written and oral assessments to select 48 peer navigators to work in pairs and implement the intervention in their areas. The peer navigator intervention mirrors the South African cadre of community caregivers.

Before the peer navigators distribute the colour coordinated HIVST packs (each arm has its designated colour such as yellow, blue and pink) with unique identifiers in the intervention arms 1 and 2 or information packs in arm 3, the packs are being scanned and study participants are provided with information about the study and fill a brief *service recipient questionnaire* to be completed within Research Electronic Data Capture (REDCap - developed by Vanderbilt University, USA)^42^ on a tablet (figure 3). Data collected at this point includes the date of recruitment, and the ID of peer navigator who recruited them, their age and area of residence. Participant’s name, ID (eg, SA national number) and telephone or WhatsApp contact are optional. Those who are recruited through RDS will also be asked to provide data on their network size, barcode of the RDS coupons and the additional HIVST kits are scanned for further distribution.

Peer navigators spend ~30 min with each willing participant to explain the benefits of linking to care and prevention. Those explaining HIVST need 15 to 20 min extra and some young people require more time or more visits. This data is captured in REDCap for the purpose of process evaluation and costing. This data will be used in an aggregate way to understand the process and cost of the service delivery. Individualised data from the survey will only be used in those participants that consent to their clinical data being linked and used for research purposes. If a participant withdraws their consent at any time, their data will be deleted from the research data set.

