Study enrolment: Both walk-ins and study participants aged 18 to 30 years are eligible for receiving services from the designated study clinics. However, only those who have been referred through one of the three arms are eligible for study enrolment. This is being conducted by trained clinical research assistants in the designated study mobile and fixed clinics (figure 4). Also, all young women aged 18 to 24 years coming to one of the 11 primary healthcare clinics (PHC) or the mobile clinics in the surveillance sites are being directed by our AHRI data collection clerks to our research nurses. In both settings, the clinical research assistants or the research nurses explain the study and screen the young person for eligibility using a brief eligibility screening questionnaire on REDCap on a tablet. This includes questions to ascertain eligibility as well as arm of the study. If available, the clinical referral slip with the barcode with the unique identifier is scanned. The brief screening questionnaire that has further simple questions to ascertain if they were referred through any of the arms, that is, receiving any of the three colour coded packs/referral slips, or contact with a named peer navigator, or referral through peer network. Interested eligible participants then go through the process of informed consent. Participants provide written informed consent for enrolment into the study and specifically to use the information on their linkage to care as an outcome and to link their baseline questions.

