### Data collection

#### Participant survey and clinic linkage

A short survey (service recipient questionnaire) is administered to consenting individuals participating in the study. The questionnaire collects data on participant’s demographic information and coupon identification. The data is captured on REDCap on a tablet. The survey takes approximately 5 min to complete and is administered in both English and isiZulu. The primary outcome of linkage is measured through identifying the consenting eligible young women who link to care through the 11 PHCs and the mobile clinics. We use an algorithm to identify which arm the individual came from, including the barcode on the referral slip they bring, the colour of the referral slips or HIVST pack, their area of residence and the identity of the peer-navigator that recruited them.

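### The clinic staff who screen and consent women ask the arm first, so the stated blinding does not hold for them, and only women who consent are counted

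*Protocol article*

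**What the plan says.** **Blinding.** The section couples the statistician with the clinical staff. Neither took part in the public randomisation, and "they will remain blinded until the results of the study have been finalised". It does not define clinical staff.

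**Study recruitment and procedures, enrolment paragraph.** In the mobile and fixed clinics and the primary healthcare clinics, "the clinical research assistants or the research nurses explain the study and screen the young person for eligibility". Of the screening form the protocol says: "This includes questions to ascertain eligibility as well as arm of the study". The questions cover "receiving any of the three colour coded packs/referral slips, or contact with a named peer navigator, or referral through peer network". On the slip: "If available, the clinical referral slip with the barcode with the unique identifier is scanned". Informed consent follows for interested, eligible women. On the packs, the recruitment paragraphs say that "each arm has its designated colour such as yellow, blue and pink". Trial design adds that the referral slips are colour coded too.

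**Who is counted.** Table 2 makes written consent a condition for ascertaining the primary outcome. Participant survey and clinic linkage says linkage is measured by "identifying the consenting eligible young women who link to care". The clinical procedures paragraph offers testing, and the counselling and screening that follow, whether or not the woman joins the study. Statistical analysis divides the count by peer-navigator time.

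**The concern.** A reader of the Blinding section would take it that the people dealing with women in the clinics do not know the arm. The enrolment paragraph has some of those people ask for it. The contradiction lies within the protocol's own text, so a separate analysis plan could not resolve it.

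It falls at a sensitive place. Consent decides whether a woman who links enters the numerator, and the staff who seek it already know her arm. If they explain the study more fully, or press harder, for one arm than another, the count changes while the true number of linkages does not. The same would happen if women reached by one route are simply more or less willing to sign. The navigator-time denominator gives no offset.

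**Working it through.** **Step 1: the texts side by side.**

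| Question | What the protocol says | Where |
|---|---|---|
| Who is said to be blinded? | Statistician and clinical staff | Blinding |
| Who screens women and explains the study? | Clinical research assistants or research nurses | Study recruitment and procedures |
| Do they learn the arm? | Yes: colour, navigator and peer-network questions, plus the slip if brought | Same |
| Before or after consent? | Before | Same |
| Is consent needed to be counted? | Yes | Table 2; Participant survey and clinic linkage |
| Can a woman who declines still link? | Yes | Study recruitment and procedures, clinical procedures paragraph |
| Does consent change the denominator? | No, it is navigator time | Statistical analysis |

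Naming the arms A, B and C does not restore masking. Referral through a peer network identifies one arm by its content, and a self-test pack as opposed to an information pack separates the other two.

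**Step 2: effect on the rate ratio.** The protocol states no figure to reproduce. For arm *a*, let L be the women who link, c the share of them who consent, and T the navigator time. The observed rate is c × L / T, so

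observed RR = true RR × (c in intervention / c in control).

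The consent shares below are assumptions.

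| Intervention v control | Ratio of shares | Observed RR if true RR = 1 | Observed RR if true RR = 2 |
|---|---|---|---|
| 90% v 90% | 0.90/0.90 | 1.00 | 2.00 |
| 90% v 80% | 0.90/0.80 | 1.13 | 2.25 |
| 95% v 80% | 0.95/0.80 | 1.19 | 2.38 |
| 90% v 60% | 0.90/0.60 | 1.50 | 3.00 |

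The direction is not fixed. With the shares reversed and no true effect, the last three rows give 0.80/0.90 = 0.89, 0.80/0.95 = 0.84 and 0.60/0.90 = 0.67.

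**Step 3: what equal loss does.** If every arm has the same share c, the ratio is unchanged. The difference in rates, which the t-test assesses, shrinks to c times its true value. At 90% in each arm it is 90% of the truth.

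**The case against.** The best case for the protocol has four parts.

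*Clinical staff may mean someone else.* The professional nurses who start PrEP or ART are described separately, and nothing says that they record or know the arm. The text does not say who carries out the PrEP screening. This stands. A reader might infer that all clinical staff are unblinded, or that the same people ask the arm and then perform the PrEP screening that makes up the outcome. The documents support neither. They also do not say that staff see the packs: staff ask about packs and handle the slip. But the arm questions alone defeat masking for those who screen and consent.

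*Care is the same in every arm.* The written workflow offers testing and counselling to all, without regard to arm or consent. This stands as far as the offer of services goes. It does not reach consent, which alone decides who is counted.

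*The consent rule is open and ethically required.* It is, and it is not an error. It is why the mistaken blinding statement has consequences.

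*No bias is shown, and the section nowhere claims that blinding protects the linkage rate.* Both are correct. A reader might also infer that, with so few linkages expected, one refusal per cluster would remove much of its count. That does not fit the shares assumed here. Sample size calculations expects one linkage per 6 months in standard of care, so one or two per cluster depending on whether this is per navigator or per pair. At 80% consent the expected loss is 0.20 × 1 = 0.2 to 0.20 × 2 = 0.4 women per cluster.

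**Conclusion.** The Blinding section is wrong at least for the clinical research assistants and research nurses who screen and consent women. Whether other clinic nurses know the arm cannot be told from the text, and the workflow figure is not available to settle it. These passages do not contradict the statistician's blinding.

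For the primary outcome this leaves an unprotected step at which the numerator is formed. Under no true effect, assumed gaps in consent of 10 to 30 percentage points give rate ratios of 1.13 to 1.50, or 0.89 to 0.67 in the other direction. A gap of zero gives 1.00. These sizes rest on consent shares that the protocol does not report, each taken as constant across the clusters of an arm. The finding is a misstatement of masking and a possible route to bias. It does not show that consent differed or that the result is biased. It should be put right, and the cost is small.

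**What to change.** 1. **Correct the Blinding section.** Claim masking only for those who have it, namely the analysing statistician working with arm codes. State that the clinic staff who screen and consent women are not masked.
2. **Report consent by arm.** Give the number of referred, eligible women aged 18 to 24 who were screened and the number who consented. Screening precedes consent, so these are aggregate screening counts. No individual outcome data on women who declined are needed.
3. **Add a sensitivity analysis.** Let s be the share of screened women who consent in an arm. If decliners link as often as consenters, divide the observed RR by the ratio of the two values of s. If no decliner links, leave it unchanged. For a wider range, let decliners link in one arm only. As an example, take an observed RR of 2.25 with s of 90% v 80%. The first case gives 2.25/1.125 = 2.00 and the second 2.25. Linking only in the intervention arm gives 2.25/0.90 = 2.50, and only in control 2.25 × 0.80 = 1.80.

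The cost is a corrected paragraph, two counts per arm and a short calculation. Use of the counts is subject to the ethics boards' agreement.

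Three other remedies look attractive but fail. Hiding the arm on the tablet does not mask someone holding a coloured slip. The colour, navigator and network questions cannot move after consent, because for women without a slip they are the eligibility check. Scanned slips from women who decline cannot be counted as linkages: the outcome is PrEP eligibility screening or ART start, and using it requires consent.

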### Sample size calculations

Based on 2017 data, we estimated ~500 age eligible 18 to 30 year olds live in each peer navigator team catchment area, of whom we anticipated at least 200, 18- to 24-year-old females will be handed a study pack (so cluster size at least 200). We estimated this based on two peer navigators working approximately 1000 hours over the study period per cluster. We estimated that they would reach two young adults per each 4 hour of work and at least one would accept a study pack. We calculated the sample size calculation using the primary outcome, the rate of linkage after 90 days among women ages 18 to 24 years. Using our existing data on uptake of HIV testing in the DREAMS interventions as well as our data on uptake of testing and linkage to HIV care in the demographic surveillance rounds of, we estimated that one woman would link per 6 months of peer navigators outreach work time in the standard of care. With eight peer educator pairs (or clusters) per arm and a cluster coefficient of variation (k) of 0.25, we will have 80% power to detect a 100% increase in rate from 1 woman to 2 women per 6 months of follow-up, and 90% power to detect a 150% increase from 1 woman to 2.5 women per 6 months of follow-up. We have chosen policy and clinically relevant increases in linkage to care. Assuming additional clustering of the outcome within peer educators and increasing the coefficient of variation (k) to 0.35, we have 80% power to detect a 150% increase in rate from 1 woman to 2.5 women per 6 months of follow-up. All sample size calculations assume two-tailed statistical tests with alpha=0.05.

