### Statistical analysis

The analysis of primary outcome follows an intention-to-treat (ITT) and per-protocol approaches. The primary outcome compares the difference between the rate of linkage of 18- to 24-year-old women to HIV confirmatory HIV testing, ART (if HIV-positive) or PrEP counselling (if HIV-negative). The rate is defined as the number of linkages per month of peer navigator outreach activities. The numerator is defined as the number of young women aged 18 to 24 who attend clinic for confirmatory HIV testing, PrEP counselling or ART, following HIVST distribution or peer navigator referral to HIV testing, treatment and prevention services. The denominator for ITT analysis is the entire time (study duration) spent by peer navigators doing their peer outreach work. For the on-treatment analysis, we will use the actual time spent by peer navigators on distributing packs in each arm. The time worked by each peer navigator will be combined to get the total time per pair of peer navigator. The difference in rate of linkage between the study arms will be calculated — incentivised HIVST delivery through peer network and direct distribution of HIVST will be compared with standard of care.

Since we randomised the pairs of peer navigator (clusters), the rate of linkage will be calculated for each pair of peer navigator using aggregate data for each cluster. Since the number of clusters are small, the effect of the intervention will be estimated using a two-stage approach based on cluster-level summaries.^45^ The cluster-level approach, although less statistically efficient than methods based on individual level regression, is more robust when there are a relatively small number of clusters. All analyses will be performed using Stata V.15 (StataCorp LP, College Station, Texas, USA).

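### The stated powers of 80%, 90% and 80% do not follow from the printed rates, cluster number and k; as printed, power for a doubling is about 31% to 50%

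*Protocol article*

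**What the plan says.** All the planning figures are in the protocol article under Sample size calculations. The control assumption is that "we estimated that one woman would link per 6 months of peer navigators outreach work time in the standard of care". The design input is "With eight peer educator pairs (or clusters) per arm and a cluster coefficient of variation (k) of 0.25". Three power statements follow:

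1. "80% power to detect a 100% increase in rate from 1 woman to 2 women per 6 months of follow-up", at k = 0.25.
2. "90% power to detect a 150% increase from 1 woman to 2.5 women per 6 months of follow-up", at k = 0.25.
3. "we have 80% power to detect a 150% increase in rate from 1 woman to 2.5 women per 6 months of follow-up", at the larger k = 0.35, which is meant to allow for extra clustering.

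The section closes with "All sample size calculations assume two-tailed statistical tests with alpha=0.05".

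Three other sections fix the exposure behind these rates. Trial design sets outreach at 6 months. Randomisation defines the cluster as one pair of navigators. Statistical analysis adds the two navigators' time: "The time worked by each peer navigator will be combined to get the total time per pair of peer navigator". The primary outcome is a rate per navigator-month.

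**The concern.** A rate of one woman per 6 months, observed for 6 months by a pair, gives one expected linkage per control cluster, or two if each navigator's time counts separately. That is 8 to 16 linkages in the whole control arm. Counts this small carry large Poisson variation whatever the value of k, and eight clusters per arm look too few to detect a doubling with 80% power.

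This is the article's only power justification for the primary outcome. If the printed rates are the true planning rates, a real doubling would be missed in about 50% to 69% of such trials, and a non-significant result would be judged against a claimed 80% power that the design lacks. If the unit is misprinted, readers would compare the observed control rate with a planning value that is wrong by a factor of six.

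**Working it through.** **Inputs.** c = 8 clusters per arm; k = 0.25 or 0.35; two-sided alpha 0.05; control rate λ0 = 1 and intervention rate λ1 = 2 or 2.5 per 6 months (all from Sample size calculations). The exposure y, in six-month units of navigator time per cluster, is not stated for the calculation. The text supports y = 1 (time per pair) or y = 2 (time per navigator, pooled as in Statistical analysis). Both are computed.

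**Formula.** The Hayes–Bennett formula for rates in an unmatched cluster trial is

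c = 1 + (z_α/2 + z_β)² × [(λ0 + λ1)/y + k²(λ0² + λ1²)] / (λ1 − λ0)².

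Solved for power:

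z_β = √{(c − 1)(λ1 − λ0)² / [(λ0 + λ1)/y + k²(λ0² + λ1²)]} − 1.96.

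**Attempt to reproduce the 80% for 1 versus 2, k = 0.25.**

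- y = 1: the bracket is 3/1 + 0.0625 × 5 = 3.3125. Then √(7/3.3125) = 1.454, z_β = −0.506, power 30.6%.
- y = 2: the bracket is 1.5 + 0.3125 = 1.8125. Then √(7/1.8125) = 1.965, z_β = 0.005, power 50.2%.

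The Poisson term (3 or 1.5) is much larger than the between-cluster term (0.3125).

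**All three statements.**

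| Comparison | k | Stated | y = 1 | y = 2 | Clusters per arm for stated power (y = 1 / y = 2) | y needed with 8 clusters |
|---|---|---|---|---|---|---|
| 1 vs 2 | 0.25 | 80% | 30.6% | 50.2% | 27 / 16 | 5.18 |
| 1 vs 2.5 | 0.25 | 90% | 51.4% | 76.2% | 20 / 12 | 3.35 |
| 1 vs 2.5 | 0.35 | 80% | 47.4% | 68.6% | 17 / 11 | 3.13 |

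The last column sets the formula equal to the stated power. For the first row, (1.96 + 0.842)² = 7.849, so the bracket must equal 7/7.849 = 0.892, and y = 3/(0.892 − 0.3125) = 5.18. The three claims need three different exposures. The best single compromise, y of about 4.2, gives 74%, 94% and 86%.

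**Is it the choice of method?**

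- Noncentral t with 14 degrees of freedom: 30.4%, 51.1%, 47.1% (y = 1) and 49.8%, 75.7%, 68.1% (y = 2).
- Gamma-Poisson simulation of the planned t-test on cluster rates, 100,000 runs: 30.0%, 51.9%, 47.4% and 49.9%, 77.7%, 70.6%.
- For the doubling: dropping the added cluster in the formula gives 34.2% (y = 1) or 55.6% (y = 2). At y = 2, no between-cluster variation at all gives 57.9%, and a one-sided test gives 62.6%.

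None of these reaches 80%.

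**Detectable effect.** At 80% power with k = 0.25, the smallest detectable intervention rate is about 3.4 women per 6 months (y = 1) or 2.6 (y = 2), against 1 in control.

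**If the rate was meant per month.** One woman per month for 6 months per pair is y = 6, which gives 83.5%, 97.4% and 90.5%. Counting both navigators (y = 12) gives 94.2%, 99.6% and 95.5%.

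**The case against.** The strongest reply has three parts.

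**The powers may be conventional minimums.** Round effects are paired with round power levels, so the figures can be read as at least 80%, 90% and 80%. One exposure then satisfies all three: at y = 5.2 the powers are 80.1%, 96.2% and 88.8%. This weakens the argument that the three figures are mutually inconsistent; that holds only if they are exact solutions. It does not rescue the text. The reading needs at least 5.2 six-month units per cluster, and nothing in the article supports that. Six months of outreach by a pair, put at about 1000 hours per cluster, supports one or two.

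**The unit may be a slip.** The primary outcome is a rate per navigator-month, and the per-month reading lifts every power above its stated value. This is quite plausible, and on that reading the design is adequate and the powers are conservative. But the six-month unit appears in the control rate and in all three comparisons, so a reader cannot know it is a misprint.

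**Exposure could be slightly higher.** Randomisation mentions three floating navigators per group besides the 16 allocated. If their time counts, which is an assumption, exposure is 19/8 = 2.375 units per cluster and power for the doubling is about 56%. So 50% is not a strict ceiling, but 80% remains far off.

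It is also fair to say that the planned rate ratios with 95% confidence intervals would show imprecision in a null result. The full protocol may name a formula and exposure, but no exposure of one or two units makes the printed figures correct.

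**Conclusion.** The concern holds. With the rates, cluster number, k and alpha as printed, the design has about 31% to 50% power for the doubling against a stated 80%, 51% to 76% against 90%, and 47% to 69% against 80%. Each range runs from one to two six-month units of navigator time per cluster, the two readings the article supports; floating navigators would raise the first to about 56%. The result does not depend on the choice of formula, and simulation of the planned test confirms it.

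This does not establish that the trial is underpowered. It establishes that the printed rate unit and the printed powers are incompatible. Either the rates were meant per month and the text is wrong by a factor of six, or the powers are overstated. The correction is essential because the primary comparison has no other power basis.

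**What to change.** State the planning rate in one unit, either linkages per navigator-month or per pair-month, and give the navigator time per cluster used in the calculation. Name the formula. Then take one of two routes:

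- **If one woman per month was intended:** change the text to 1 versus 2 and 1 versus 2.5 women per month, and give the resulting powers. For 6 months counted per pair these are 84%, 97% and 91%; for 12 navigator-months they are 94%, 99.6% and 95.5%.
- **If one woman per 6 months is correct:** replace the three powers with the recomputed ones, or restate the effect detectable with 80% power at k = 0.25 as a rate of about 3.4 (time per pair) or 2.6 (time per navigator) times control.

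Carry the same figures into the statistical analysis plan. The cost is a text correction, with no added clusters and no change to conduct. On the second route the stated power or detectable effect becomes less favourable.
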